### 1462 *9.3 Definition of Populations*

1463 ITT (Intent to treat) refers to all participants who have completed the baseline assessments and have  
1464 been randomized to 1 of 2 arms.

1465 Modified ITT refers to all participants who have attended at least one session and completed the  
1466 measure at the screening and baseline visits.

1467 Per treatment refers to participants who have completed (no more than 3 missed sessions) either VA or  
1468 PA and the assessments (both baseline and post-treatment visits).

### 1469 *9.4 Interim Analyses and Stopping Rules*

1470 The most common risks in acupuncture are local swelling, bruising, and pain, and less commonly  
1471 transient nausea and dizziness.

1472 We do not anticipate that safety reviews will be necessary unless we see clear harm (>50% worse from  
1473 baseline for one group, or >50% participants experience prolonged (>2 weeks) moderate or severe side  
1474 effects (eg nerve injury, large hematoma with diameter > 5cm, or increased back symptoms that prevent

the participant from tending to normal work and recreational activities which were not a problem prior to participating in the study). Such findings will be reported to the PI and the lab manager to review the events by group to determine whether there are statistical as well as clinical concerns. The research team will report the findings to NCCIH. The findings are used to determine what steps will be taken, such as to determine whether the project should continue per protocol, proceed with caution, be further investigated, be discontinued, or be modified and then proceed.

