#### **5.4.2 Daily Questions**

One secondary objective of the study is to delineate the time to response to electroacupuncture. Though not able to obtain hourly ratings of pain after the treatment, we will be able to collect daily measures of average pain and physical function electronically via REDCAP. The patient will be reminded to fill out this very brief questionnaire (2 questions) daily via a text to their smart phone or an email if the patient does not have access to a smart phone. Additionally, we will collect information weekly via another brief questionnaire on the side effects from the study interventions as well as other treatments obtained by the patient for back pain. This weekly questionnaire will be administered in a similar fashion as the brief daily questionnaire.

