#### 6.2.3 Blinding

Blinding of the participant will be ensured by strict controls in the communications between the acupuncturist and the participant. The acupuncturists will receive one day of hands-on training as well as written materials, and they will attend a refresher workshop 1-2 weeks before seeing their first participants. Strict guidelines on communication with the participant will be provided and will be reinforced during regular provider meetings with the PI ([name]).

Blinding of the assessor. The PI and the research assistant will be the assessors. Only the acupuncturists (treatment providers) will be unblinded. The randomizer will deliver the randomization assignment to the acupuncture provider via secure email.

1183 Individuals authorized to break the blind. The members from the DSMB will meet and assess side  
 1184 effects from both treatment arms and decide if there is a need to unblind and to possibly terminate or  
 1185 modify the problematic treatment.

1186 Circumstances for breaking the blind: We do not anticipate that we will need to break the blind unless  
 1187 we see clear harm (>50% worse from baseline for one group, or >30% participants experience prolonged  
 1188 side effects, e.g. severe pain, persistent hematoma, nausea etc) lasting over two weeks.

1189 Procedures for breaking the blind. We stress that we do not anticipate breaking the blind except for  
 1190 extenuating circumstances where significant harm is caused by the VA or PA treatment. Such  
 1191 circumstances will always be reported to the DSMB and a decision regarding how to proceed will come  
 1192 from the DSMB. Such examples include a) large bleeding and bruising (over three sessions) due possibly  
 1193 to an undiagnosed clotting disorder; b) severe pain due to the treatment as recorded on the participants  
 1194 weekly adverse event report form lasting more than two weeks; c) unresolved nausea, dizziness  
 1195 persistent for more than two weeks.

1196 In terms of procedures for breaking the blind, we will use the following steps.

1197 **Level 1:** The research assistant will be responsible for monitoring the participant's adverse event data  
 1198 gathered via the Android device; additionally, the acupuncturist will monitor and report on side effects  
 1199 from treatment. If any of the above mentioned severe reactions to acupuncture occur (extremely rare),  
 1200 the RC and/or the acupuncturist will report to the PI.

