1342 present at baseline, appears to worsen. Adverse events are to be recording regardless of their  
1343 relationship to the project intervention.

1344 A **serious adverse event (SAE)** is generally defined as any untoward medical occurrence that results in  
1345 death, is life threatening, requires inpatient hospitalization or prolongation of existing hospitalization,  
1346 results in persistent or significant disability/incapacity, or is a congenital anomaly.

1347 The participants will be provided with emergency phone numbers to contact the team in case of serious  
1348 side effects.

1349 At each treatment visit, the acupuncturists will record all adverse events in the Adverse Events CRF and  
1350 will notify the Clinical Core.

1351 The daily questions completed by participants on Androids will capture participant mood as well as  
1352 common side effects. Triggers will be programmed into the application for a negative mood rating,  
1353 which will alert the Clinical Core after 5 consecutive reports of greater than 30% negative change in  
1354 mood as compared to baseline. The Clinical Core will then follow-up with the participant by phone to  
1355 inquire about the negative mood rating and record it in the Adverse Event CRF.

1356 Finally, there will be a short questionnaire programmed into the Android device to ask about side effects  
1357 and adverse events at the end of each week. The Clinical Core will monitor these weekly reports and

1358 follow-up with the participant by phone if side effects are reported and an Adverse Event CRF will be  
1359 completed for the participant's record.

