#### 1388 **7.6 Safety Monitoring**

##### 1389 **Data Monitoring and Safety Board (DSMB)**

1390 The CAM Center DSMB has the following members:

1391 [name], PhD (Biostatistics expertise)

1392 [name], PhD (TCM trials expertise)

1393 [name], MD/PhD (Clinical expertise)

1394 The DSMB will convene every 3 to 6 months after initial recruitment. Safety will be reviewed and  
1395 participant cases will be reported to the members of the DSMB and relevant safety decisions will be

1396 made. The sessions will be open to PI and the mentors. DSMB reports will be sent to NCCIH and Stanford  
1397 IRB within 10 business days of the meeting.

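### Sections 6.2.3 and 9.4 give the aggregate 'clear harm' rule different side-effect limits and different reviewers, and the protocol contradicts itself on where the mood trigger's data come from

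*Protocol*

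**What the plan says.** **Aggregate rule.** Section 6.2.3 (Blinding) says the blind is not expected to be broken unless "we see clear harm (>50% worse from baseline for one group, or >30% participants experience prolonged" "side effects, e.g. severe pain, persistent hematoma, nausea etc) lasting over two weeks". DSMB members assess side effects from both arms and decide whether to unblind and whether to terminate or modify a treatment. The same section makes the PI an assessor and says only the acupuncturists are unblinded; 10.2 repeats that the PI is blinded.

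Section 9.4 (Interim Analyses and Stopping Rules) does not anticipate safety reviews unless there is clear harm. It uses the same first limb and then "baseline for one group, or >50% participants experience prolonged (>2 weeks) moderate or severe side" effects, with nerve injury, a haematoma over 5 cm and disabling back symptoms as examples. On routing it says: "Such findings will be reported to the PI and the lab manager to review the events by group". NCCIH is then informed, and the findings feed a choice among continuing, modifying or discontinuing the project. The DSMB is not mentioned.

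Section 7.6 provides for regular review: "The DSMB will convene every 3 to 6 months after initial recruitment", with safety reviewed.

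**Mood trigger.** Section 7.3 says: "The daily questions completed by participants on Androids will capture participant mood as well as" common side effects, and that staff are alerted after 5 consecutive reports of more than 30% worsening from baseline. Section 8 lists negative mood ratings, monitored by Android device, among the grounds for withdrawal. Section 5.4.2 says participants will "fill out this very brief questionnaire (2 questions) daily", covering average pain and physical function through REDCap. The Précis lists pain, sleep and function as the daily content.

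**The concern.** The two definitions share a name and a first limb, so they read as one rule. They part at the percentage, the severity wording and the body that acts. A trial team whose event rate fell between the two limits would find unblinding under consideration in one section and no reason for a review in the other. Neither section gives a denominator for the side-effect limb, so two people counting the same data could also disagree on whether either limit had been reached.

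Review by group by a PI who is a blinded assessor needs an explanation that 9.4 does not give. The primary outcome is self-reported pain, collected at visits that the PI or research coordinator conducts, so the assessor's blind matters to the result.

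The mood trigger is a stated protection with a numerical threshold, yet the sections that describe the daily survey's content do not list the item it needs.

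**Working it through.** **1. The side-effect limbs side by side**

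| | 6.2.3 | 9.4 |
|---|---|---|
| Attached to | breaking the blind | holding a safety review |
| First limb | >50% worse from baseline, one group | the same |
| Side-effect percentage | >30% | >50% |
| Duration | over two weeks | over two weeks |
| Severity | no overall grade; examples include nausea | moderate or severe |
| Denominator | not stated | not stated |
| Who acts | DSMB decides | PI and lab manager review by group; DSMB not named |

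**2. Percentages as counts.** The inputs are 100 participants in all and 50 per arm (9.2). The smallest count strictly above a fraction p of N is floor(pN) + 1.

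- N = 100: floor(30) + 1 = 31; floor(50) + 1 = 51.
- n = 50: floor(15) + 1 = 16; floor(25) + 1 = 26.

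If both limits count the same events, they disagree from 31 to 50 affected of 100, or from 16 to 25 of 50. These are counts at full enrolment.

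**3. Effect of the severity wording.** Let A be the number with prolonged side effects of any grade and B the number with moderate or severe ones, so B ≤ A. Over all 100 participants, 6.2.3 is met at A ≥ 31 and 9.4 at B ≥ 51. They disagree whenever A ≥ 31 and B ≤ 50. With A = B this is 31 to 50. With B below A it extends further: A = 60 and B = 20, for example, meets 6.2.3 and not 9.4. So 50 is not an upper bound on A.

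**4. How often the limits would differ.** With X ~ Binomial(N, π), the chance of crossing a limit k is P(X ≥ k). The true rates π are assumptions, as is a common event definition; the protocol gives neither.

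| π | N=100: >30% | N=100: >50% | n=50: >30% | n=50: >50% |
|---|---|---|---|---|
| 20% | 0.006 | <0.001 | 0.031 | <0.001 |
| 30% | 0.451 | <0.001 | 0.431 | <0.001 |
| 40% | 0.975 | 0.017 | 0.905 | 0.057 |
| 50% | 1.000 | 0.460 | 0.997 | 0.444 |

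At 20% neither limit is likely to be reached and the conflict has little effect. From about 30% upward, which section is followed largely decides the outcome.

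**5. Sources for a mood rating during treatment.**

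- 5.4.2: two daily questions, pain and physical function.
- Précis: pain, sleep and function daily.
- 6.2.1: daily back pain and unspecified related symptoms; weekly adverse events, pain locations and new treatments.
- 6.1: PROMIS depression and anxiety at the pre- and post-treatment visits; PH-9 at screening.
- 7.3 and 8: mood, daily, on an Android device.

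Only 7.3 and 8 name a daily mood item. The platform differs too: REDCap in 5.4.2 and 10.1, Android in 6.2.3, 7.2, 7.3, 8 and 10.3.3.

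**The case against.** **The limits serve different actions.** One governs unblinding and the other a safety review, so they need not be equal. That is true in form. But both are given as the meaning of the same term, and the limit for the more drastic step is the lower one. The conflict stands.

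**Participants are protected regardless.** Under 7.4, severe related events go to the DSMB at once and treatment is stopped. Section 7 alerts the DSMB to infection, nerve injury or pneumothorax. Section 6.2.3 sets a route from coordinator or acupuncturist to PI to DSMB, and 7.6 has the DSMB meeting regularly. This stands. A reader might infer that nobody knows who acts on harm, or that the blind could be broken with no review at all. The documents do not support either: the individual-event route is defined, and under 6.2.3 the DSMB assesses both arms before any unblinding.

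**Section 9.4 omits the DSMB rather than overruling it.** It does not say who takes the final decision, and in 6.2.3 the PI also hears first. This is partly right, and it narrows the point to an unreconciled reviewer for the aggregate rule.

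**Section 9.4 does not say the PI is unblinded.** A reader might infer that it does. Review by group could use coded groups, and the lab manager named beside the PI is linked elsewhere to running the randomization (4.3.2, 9.2) and de-identifying data (10.2). The text neither provides for coding nor excludes it, so this is an unexplained tension with the blinded role and not an established unblinding.

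**Section 7.3 itself says mood is captured.** It does, 6.2.1 is vague, and the survey form is not in the protocol. A reader might infer that the mood alert can never fire. That would take 5.4.2 as definitive, although the Précis already adds sleep to its two items. What can be said is that 7.3 and 8 contradict 5.4.2 and the Précis.

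**Conclusion.** The inconsistency is real and should be fixed. It covers the aggregate harm rule and the data source for the mood trigger; it does not cover safety oversight as a whole.

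The 31-to-50 range (16 to 25 in one arm) rests on counting the same events for both limits at full enrolment. The severity wording differs, so the range is not a fixed bound and the real zone of disagreement could be wider. The crossing probabilities rest on assumed event rates. Section 7 describes the common side effects as minor and typically gone within 2 to 3 days, so rates near these limits are not what the protocol expects. That expectation, the separate route for individual severe events and the absence of any direct effect on the primary analysis make this a should-fix and not a must-fix.

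On mood, the conclusion stops at a contradiction between sections. Whether the survey actually used had a mood item cannot be determined from the protocol.

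**What to change.** Amend the wording in two places.

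1. Reconcile 6.2.3, 7.6 and 9.4 into one aggregate rule, stated once and cross-referenced. It needs one percentage, one severity and duration qualifier, one denominator (per arm or overall) and one named reviewing body. State how by-group review is kept consistent with the PI's blinded role, and make the remark in 9.4 about safety reviews agree with the DSMB schedule in 7.6. If unblinding and safety review are meant to have different limits, say so and give each its own name.
2. Reconcile the daily-survey content and platform in 5.4.2, 6.2.1 and the Précis with the mood trigger in 7.3 and 8, so that the trigger refers to an item and a system the protocol describes.

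Which threshold, reviewer and mood rule apply is for the sponsor and the DSMB. The cost is amendment text and, if a mood item turns out to be wanted and missing, at most one extra daily question. Sample size and the primary analysis are unaffected.

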## 9.5 Outcomes

### 9.5.1 Primary Outcome

**Primary outcome:** Change in Pain Intensity measured by the T-scores computed from the full PROMIS Pain Intensity Instrument administered at the pre-treatment and post-treatment visit.

### 9.5.2 Secondary Outcomes

**Secondary outcomes:** a) percent pain reduction at 6 and 12 months from baseline; b) percent change in physical function, measured by RMDQ or the pain interference instrument from PROMIS at the post-treatment visit, and at 3, 6 and 12 months from baseline. C) percent change in pain intensity measured by the 11-point NRS at both the pre- and post- treatment visit.

## 9.6 Data Analyses

**Aim 1. Explore the predictive relationship and the association between ascending sensitization measures and clinical response to acupuncture.**

**Planned analysis:** There are two specific goals of the analysis: (1) explore the predictive relationship between key baseline parameters and treatment response (pain reduction) accordingly by arm; and (2) examine the associations between baseline predictors and treatment response by arm. The identified association can help us understand the underlying mechanism of the treatment effect from acupuncture and, AND assist in building good subsequent prediction models. To this end, taking temporal summation (TS) first as an example, we will first estimate the correlation coefficients between baseline TS and the primary outcome (% pain reduction immediately after treatment) and then perform multivariate linear regression with clinical pain reduction as the continuous dependent variable and TS and potential confounding factors such as the demographic variables and the baseline pain level as independent variables in the verum arm. We will estimate the regression coefficients and their 95% confidence intervals, which will be used to formally test association between TS and pain reduction with or without adjustment of potential confounders. To evaluate the predictiveness of TS (with other patients' characteristics) to pain reduction, we will also calculate the mean squared prediction error of the multivariate regression model. Variable selection method such as lasso may be used to remove unnecessary predictors from the model and cross-validation will be used to estimate the prediction accuracy to account for the adaptive model building step. Likewise, we will repeat the analysis in the sham arm. Specifically, we will test the presence of the association by examining if zero is inside the interval for confirming the hypothesis that the association is close to null in the sham arm. We will also estimate the interaction between the treatment group and TS to determine if decreased TS better predicts treatment response to verum than to sham acupuncture. Note that factors which are equally predictive to the pain reduction in both arm in general do not have interaction with the treatment.

1514 In summary, the primary objective will be to assess the predictiveness of baseline TS to pain reduction;  
1515 and the primary outcome of pain reduction will be the difference in pain between baseline and  
1516 immediately after treatments. The primary analyses will be the computation of mean-squared  
1517 prediction error from a multivariate regression model, as well as the use of Lasso and cross-validation to  
1518 improve and validate the predictive model with TS. The second objective will be to quantify the  
1519 association between TS and pain reduction immediately after treatments (ie secondary outcome is the  
1520 same as the primary outcome, pain reduction immediately after treatments). The secondary analyses  
1521 will be a) computation of the correlation coefficient between baseline TS and pain reduction and b)  
1522 estimation of the regression coefficient and 95% confidence intervals between baseline TS and pain  
1523 reduction in a multivariate regression model taking TS and other baseline variables into account.

1524 The same analyses will be applied to pressure pain threshold and widespread pain. Realizing that pain  
1525 reduction may not be normally distributed and that the assumed linear regression model may not be  
1526 appropriate, we will repeat the above analysis using a conservative, semi-parametric transformation  
1527 model. We will perform the parallel logistic analysis with dichotomized pain-reduction (responder vs  
1528 non-responder) as the binary dependent variable of interest. We will perform similar analyses for  
1529 widespread pain. Finally, we will repeat the above using pain reduction at 6 months post-treatment as  
1530 our outcome variable.

1531 **Aim 2. Explore the predictive relationship and the association between descending pain modulatory**  
1532 **measures and clinical response to acupuncture.**

1533 **Planned analysis:** the statistical plan for Aim 2 is almost identical to that of Aim 1 except, we replace  
1534 baseline factors of TS, pressure pain threshold and widespread pain, with baseline CPM, pain  
1535 catastrophizing, coping effectiveness and self-efficacy. In summary, the primary objective will be to assess  
1536 the predictiveness of baseline descending pain modulatory factors (CPM, pain catastrophizing, coping  
1537 effectiveness and self-efficacy for pain management) to pain reduction; and the primary outcome of  
1538 pain reduction will be the difference in pain between baseline and immediately after treatments. The  
1539 primary analyses will be the computation of mean-squared prediction error from a multivariate  
1540 regression model, as well as the use of Lasso and cross-validation to improve and validate the predictive  
1541 model with each descending pain-modulatory factor of interest. The second objective will be to quantify  
1542 the association between each descending pain-modulatory factor of interest and pain reduction  
1543 immediately after treatments (ie secondary outcome is the same as the primary outcome, pain  
1544 reduction immediately after treatments). The secondary analyses will be a) computation of the  
1545 correlation coefficient between each baseline descending factor and pain reduction and b) estimation of  
1546 the regression coefficient and 95% confidence intervals for between each baseline descending factor of  
1547 interest and pain reduction in a multivariate regression model.

1548 Finally, recognizing the exploratory nature of our study aims, we appreciate the fact any significant  
1549 findings from the analyses from both Aim 1 and Aim2 may be due to artifacts of multiple looks at the  
1550 data. Therefore, we will a) consider correction for multiple comparisons in our final analysis; b) verify  
1551 the significant findings from our pilot exploratory study in subsequent, larger, controlled clinical trials.

1552 **Aim 3. Exploratory model building. I will explore mathematical models relating acupuncture analgesia**  
1553 **to baseline characteristics, and test this model within the proposed pilot via cross-validation.**

1554 **Planned analysis: Model-building.** We will train a predictive model based on all factors examined in  
1555 Aims 1 and 2, and additional baseline measures including demographics, job status, history of childhood  
1556 trauma (PTSD), fear avoidance beliefs, and current symptoms of mood disorders. We will develop  
1557 multivariate prediction models for predicting pain-reduction after treatment. Lasso-penalized  
1558 logistic/linear regression, regression tree, random forest, boosted CART, and other data mining  
1559 techniques will be employed. Using cross-validation, we will check the quality of our models by mean-  
1560 squared prediction error for continuous outcome; and by misclassification error and  
1561 sensitivity/specificity in the ROC curves for dichotomized outcomes. The prediction model will be trained  
1562 in the verum and sham arms separately. In the end, we will balance simplicity, interpretability and the  
1563 prediction performance to select the optimal model, where the prediction performance will be  
1564 objectively evaluated again with cross-validation. The final constructed models can be used for guiding  
1565 and developing personalized delivery of acupuncture.

1566 Validation. We will test the performance of the selected prediction model on patients via cross-  
1567 validation by comparing the observed and predicted outcome. The performance will be evaluated via  
1568 metrics, including mean-squared error, misclassification rate, sensitivity, specificity, and ROC curve,  
1569 when appropriate. Importantly we will predict the treatment benefit of each patient using the chosen  
1570 models and will identify the subgroup of patients with the highest predicted benefit of verum relative to  
1571 sham. Then we will estimate the treatment effect in the identified subgroup of patients. If the actual  
1572 pain reduction in verum arm is significantly higher than sham among the selected subgroup of patients,  
1573 then the selected model will be deemed successful and may be used for recommending acupuncture in  
1574 clinical practice.

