## **1. STUDY OBJECTIVES**

### **1.1 Primary Objective**

**Aim 1.** Explore the predictive relationship and the association between *ascending sensitization* measures and clinical response to acupuncture.

*Hypothesis 1: augmented temporal summation (TS), and more wide-spread pain (WSP) (quantified by number of painful areas marked by the participant on a standardized body map) will be associated with greater pain reduction in the verum arm than in the placebo arm; decreased pressure pain threshold (PPTr) will be associated with greater pain reduction in the placebo arm than the verum arm.*

*Aim 2. Explore the predictive relationship and the association between **descending modulatory** measures and clinical response to acupuncture.*

*Hypothesis 2: decreased conditioned pain modulation (CPM), and more favorable psychological state, measured by less pain catastrophizing, better self-efficacy in coping and in pain management, will be associated with greater pain reduction in the verum than the placebo arm; expectation of positive treatment outcome will be associated with pain reduction in both the verum and the placebo arm.*

*Aim 3. **Exploratory model building** to predict pain reduction by electroacupuncture.*

*Hypothesis 3. A mathematical model relating key baseline characteristics to percent pain reduction will be developed using advanced techniques, and this model will be tested using cross-validation within the proposed pilot.*

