#### 1435 *Power Analysis*

1436 The objectives of aim 1 are to 1) explore the predictive relationship between ascending factors of  
1437 interest and pain reduction due to our interventions; 2) test the association between the ascending  
1438 factors and pain reduction. However, because the former is exploratory in nature, we will design our  
1439 study to power for the latter objective. Specifically, we compute the number of patients needed to find  
1440 an association between key baseline parameters (pressure pain threshold, temporal summation (TS), or  
1441 widespread pain) and pain reduction due to verum treatment. With 50 patients per arm, we will be able  
1442 to detect a moderate correlation of 0.4 (supported by literature for pressure pain threshold and TS)  
1443 with approximately 80% power with alpha of 0.05 using Fisher's transformation. Next, to determine if  
1444 the association is stronger in the verum than the sham arm, we will test the interaction between  
1445 treatment and the baseline parameters. Fifty patients per arm will provide 80% power (with alpha of  
1446 0.05) to detect a moderate difference of 0.5 between correlation from the verum arm and that from the  
1447 sham arm. Therefore, we are adequately powered to detect a moderate association between baseline  
1448 parameters and the clinical response in the verum acupuncture arm and a moderate difference in the  
1449 strengths of these associations between the verum and the sham treatment group.

1450 Similar calculation with identical numbers can be found for aim 2 (descending factors). Note prior  
1451 literature supports a moderate association around 0.4 between catastrophizing and pain reduction as  
1452 well as between self-efficacy and pain reduction in patients suffering from chronic low back pain.

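### Section 9.6 takes a 95% interval covering zero as confirmation of a near-null sham association, with no margin, and its interaction sentence reverses the temporal summation direction of Hypothesis 1

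*Protocol*

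**What the plan says.** Section 9.6 uses temporal summation (TS) as the worked example for Aim 1. On estimation and testing it says: "We will estimate the regression coefficients and their 95% confidence intervals, which will be used to formally test association between TS and pain reduction". The analysis is repeated in the sham arm, where the association is tested by "examining if zero is inside the interval for confirming the hypothesis that the association is close to null in the sham arm". The following sentence plans a treatment-by-TS interaction to "determine if decreased TS better predicts treatment response to verum than to sham acupuncture". After the TS summary, the section adds: "The same analyses will be applied to pressure pain threshold and widespread pain".

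The hypotheses are in section 1.1 and are repeated in section 9.1. Hypothesis 1 names "augmented temporal summation (TS), and more wide-spread pain (WSP" as going with greater pain reduction in verum than in placebo. For decreased pressure pain threshold the order is the other way: it "will be associated with greater pain reduction in the placebo arm than the verum arm". 

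The power analysis in section 9.2 begins "With 50 patients per arm, we will be able". It gives about 80% power for a correlation of 0.4 in one arm, and it names the interaction test as the way to establish that an association is stronger in verum than in sham.

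**The concern.** There are three linked faults in one paragraph.

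- **Accepting the null.** A confidence interval that includes zero is compatible with no association, but also with every other value it contains. To support a near-null claim, the whole interval must lie inside a stated margin, and the protocol gives none. The rule also rewards imprecision: the fewer evaluable sham patients there are, the more easily it is met.
- **A hypothesis that is not among the hypotheses.** Hypothesis 1 says the TS association is greater in verum than in placebo. Neither hypothesis says it is absent in placebo. For pressure pain threshold, Hypothesis 1 expects the stronger association in placebo, so carrying the sham rule over sets out to confirm something close to the opposite.
- **Direction.** The interaction sentence and Hypothesis 1 point TS in opposite directions.

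At stake is a false statement that a predictor has no bearing on response to sham acupuncture, and uncertainty over which sign of the TS interaction was specified in advance.

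**Working it through.** **Inputs.** n = 50 per arm and a moderate correlation of 0.4 (section 9.2); 95% intervals (section 9.6). Two-sided alpha of 0.05 is assumed, to match the 95% interval, because section 9.2 does not state sidedness. The calculation treats the unadjusted correlation; the adjusted regression interval would need covariate information that the protocol does not give.

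**The plan's own figure first.** On Fisher's z scale the standard error is 1/√(50 − 3) = 1/√47 = 0.146. Power at a correlation of 0.4 is Φ(atanh(0.4) × √47 − 1.96) = Φ(2.904 − 1.96) = 82.8%. This agrees with the stated approximate 80% and errs on the safe side. It is not in dispute.

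**What passes the rule.** Zero is inside the interval when |atanh(r)| < 1.96 × 0.146 = 0.286, that is |r| < tanh(0.286) = 0.278.

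- At that boundary the upper limit is tanh(2 × 0.286) = 0.52.
- At an observed r of 0.20 the interval is −0.08 to 0.45.

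Both intervals contain 0.4, yet both would count as confirming a null.

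**How often the rule declares a null.** With m = atanh(ρ) × √(n − 3), P(zero in interval) = Φ(1.96 − m) − Φ(−1.96 − m).

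| True ρ | m at n = 50 | n = 50 | n = 40 (assumed evaluable) |
|---|---|---|---|
| 0.1 | 0.688 | 89% | 91% |
| 0.2 | 1.390 | 72% | 77% |
| 0.3 | 2.122 | 44% | 53% |
| 0.4 | 2.904 | 17% | 27% |

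A simulation of the corresponding t test (100,000 runs, n = 50) gave 71%, 43% and 16% at 0.2, 0.3 and 0.4. The n = 40 column is an illustration only, since the power section states no dropout rate.

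**Could a proper near-null claim be made instead?** Take an equivalence test at one-sided 0.05 with 80% power when the true correlation is zero, so that n = ((1.645 + 1.282)/atanh(margin))² + 3. The sham arm would need about 93 patients for a margin of ±0.3 and 212 for ±0.2. With 50 patients, power is about 37% for ±0.3. For ±0.2 it is nil, because the 90% interval has half-width tanh(1.645 × 0.146) = 0.235 even at an observed correlation of zero. These margins are assumptions.

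**Hypotheses against section 9.6.**

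| Predictor | Hypothesis | Null sham association compatible? |
|---|---|---|
| TS | greater in verum | yes, but not stated; direction reversed in 9.6 |
| Widespread pain | greater in verum | yes, but not stated |
| Pressure pain threshold | greater in placebo | no |
| Aim 2 predictors listed in 9.6 | greater in verum | yes, but not stated |

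**The case against.** The best defence is that the valid comparison is already planned. Section 9.2 says the interaction will decide whether an association is stronger in verum. Section 9.6 plans it directly after the disputed sentence and notes that equally predictive factors generally show no interaction. Section 9.6 also classes the correlation and regression-interval work as secondary, behind prediction error with lasso and cross-validation. It calls the aims exploratory and promises verification in larger trials. All of this stands and limits the damage. It does not make the sham rule valid: the caution in 9.6 concerns significant findings, not false nulls.

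On pressure pain threshold, the null-in-sham sentence sits inside a TS example, and the summary before "The same analyses will be applied to pressure pain threshold and widespread pain" does not repeat it. The conflict therefore depends on reading that instruction literally. That is a fair qualification, and a reason to clarify the text.

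Three stronger readings are tempting but not supported:

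- A reader might infer a conflict with Hypothesis 2, which says "expectation of positive treatment outcome will be associated with pain reduction in both the verum and the placebo arm". But the Aim 2 list in 9.6 contains conditioned pain modulation, catastrophizing, coping effectiveness and self-efficacy. Expectation is not in it, so the rule is not expressly applied there, and the listed predictors are compatible with a null in sham.
- A reader might infer that significance in verum with a null in sham will be reported as specificity to real acupuncture. If both arms truly had a correlation of 0.4, that pattern would arise 0.828 × 0.172 = 14% of the time. The protocol states no such combined rule, so this figure illustrates a risk and is not a property of the plan.
- A reader might infer that the TS wording lets either sign be claimed. Sections 1.1 and 9.1 agree on augmented TS, so a drafting slip in 9.6 is the more plausible explanation.

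**Conclusion.** The sham-arm confirmation rule is wrong as written, and the TS direction in 9.6 contradicts Hypothesis 1. With 50 patients the rule would declare a null about 72%, 44% and 17% of the time at true correlations of 0.2, 0.3 and 0.4. The conflict with the stated hypotheses is confined to pressure pain threshold under Hypothesis 1; Hypothesis 2 is not contradicted.

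The figures rest on the unadjusted correlation, two-sided 0.05 and all 50 sham patients being evaluable. Fewer evaluable patients make a false null more likely.

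Severity is moderate. The primary outcome, the sample size and the planned interaction test are unaffected, but the text pre-specifies an invalid inference on the predictor that serves as the template for the rest of Aim 1.

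**What to change.** In section 9.6, Aim 1:

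1. Delete the rule that zero inside the interval confirms a near-null sham association.
2. Report the sham association with its 95% confidence interval and make no null claim from it.
3. State that every verum-versus-sham claim rests only on the treatment-by-predictor interaction already planned in 9.2 and 9.6, with its 95% interval. For pressure pain threshold, say that the expected difference favours the placebo arm, as in Hypothesis 1.
4. Make the TS direction in the interaction sentence match Hypothesis 1 in sections 1.1 and 9.1.

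The cost is rewording one paragraph before analysis, with no new data or analyses. The interaction interval will be wide: for two arms of 50 its half-width on Fisher's z scale is 1.96 × √(2/47) = 0.40. An inconclusive interaction should be reported as inconclusive.
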